## Abstract

**Background:**

Nerve root decompression with instrumented spondylodesis is the most frequently performed surgical procedure in the treatment of patients with symptomatic low-grade spondylolytic spondylolisthesis. Nerve root decompression without instrumented fusion, i.e. Gill's procedure, is an alternative and less invasive approach. A comparative cost-effectiveness study has not been performed yet. We present the design of a randomised controlled trial on cost-effectiveness of decompression according to Gill versus instrumented spondylodesis.

**Methods/design:**

All patients (age between 18 and 70 years) with sciatica or neurogenic claudication lasting more than 3 months due to spondylolytic spondylolisthesis grade I or II, are eligible for inclusion. Patients will be randomly allocated to nerve root decompression according to Gill, either unilateral or bilateral, or pedicle screw fixation with interbody fusion. The main primary outcome measure is the functional assessment of the patient measured with the Roland Disability Questionnaire for Sciatica at 12 weeks and 2 years. Other primary outcome measures are perceived recovery and intensity of leg pain and low back pain. The secondary outcome measures include, incidence of re-operations, complications, serum creatine phosphokinase, quality of life, medical consumption, costs, absenteeism, work perception, depression and anxiety, and treatment preference. The study is a randomised prospective multicenter trial in which two surgical techniques are compared in a parallel group design. Patients and research nurse will not be blinded during the follow-up period of 2 years.

**Discussion:**

Currently, nerve root decompression with instrumented fusion is the golden standard in the surgical treatment of low-grade spondylolytic spondylolisthesis, although scientific proof justifying instrumented spondylodesis over simple decompression is lacking. This trial is designed to elucidate the controversy in best surgical treatment of symptomatic patients with low-grade spondylolytic spondylolisthesis.

## Background

Spondylolytic spondylolisthesis is an anterior slip of one vertebral body onto another caused by a discontinuity (lysis) of the pars interarticularis, also called the isthmus. As a result of the pseudarthrosis, fibrocartilaginous tissue develops at the isthmic site. Although most people with spondylolytic spondylolisthesis are asymptomatic, patients may present with low back pain, sciatica, neurogenic claudication, or a combination due to nerve root compression in the parapedicular course under the fibrocartilaginous mass of the pseudo-joint, or at the neuroforamen between the pedicle and slipped disc.

Treatment of patients with symptomatic spondylolytic spondylolisthesis consists of nonsurgical management or surgery whereby surgery yields better outcome [1]. Surgical management comprises primary reconstruction of the pars interarticularis defect, decompression of the nerve root without fusion, decompression with (instrumented) spondylodesis, or a combination. Transpedicular fixation with interbody fusion is the most frequently advocated surgical technique [2-9].

A less invasive approach, in which nerve root decompression is performed without fusion, has been described by Gill [10]. The operation according to Gill consists of removing the loose lamina and excising the fibrocartilaginous tissue in order to decompress the nerve root. Various studies have reported satisfactory results [11-13]. Recently, we have presented the long-term results of 42 patients treated with bilateral nerve root decompression according to Gill or unilateral decompression; i.e. hemi-Gill. At 11 years after surgery improvement of leg pain was reported in 88%, and 71% documented good result in terms of patient satisfaction [14].

Although most surgeons perform nerve root decompression with instrumented fusion in the treatment of spondylolytic spondylolisthesis, scientific proof justifying instrumented spondylodesis over simple decompression is lacking. The clinical results of instrumented and noninstrumented spondylodesis seem comparable with decompression according to Gill; 60 to 90% of the patients have good results [4,6,15-20]. The main arguments that favour intercorporal instrumented fusion are enlargement of the neuroforamen to relieve nerve root compression, and prevention of progressive slippage. Instrumented spondylodesis, on the other hand, constitutes major surgery with considerable blood loss, longer operation time, and significant complication rates which correlate with the extent of fusion [19,21,22].

Gill's procedure is a less invasive alternative technique to instrumented fusion. The operation time is shorter and the paraspinal muscle injury is less extensive. Patients may have less surgery-related low back pain and mobilise quickly, indicating short hospitalisation, fast recovery and early resumption to work. In addition, costs and complications related to instrumented surgery are avoided. However, secondary instrumented surgery might be necessary in patients with recurrent or persisting leg pain due to foraminal nerve root compression [14].

The controversy in the treatment of low grade spondylolytic spondylolisthesis justifies a randomised controlled trial comparing instrumented spondylodesis with nerve root decompression alone. The purpose of our study, the Sciatica-Gill trial, is to assess the clinical outcome and cost effectiveness of both surgical strategies on the short term (12 weeks) and long term (2 years). There will be a trade-off between persisting or recurrent leg pain in the Gill group and higher complication rates and costs in the spondylodesis group. Secondly, various subgroups of patients will be identified who may benefit primarily from one of the allocated surgical treatments.

## Methods/design

We designed a multicenter randomised controlled cost-effectiveness trial on the treatment of low-grade spondylolytic spondylolisthesis in which two surgical techniques are compared in a parallel group design. The primary outcome measure is the Roland Disability Questionnaire (RDQ) for sciatica. The follow-up period will last 2 years (with extension to 5 years). In order to collect enough patients, a multicenter design is necessary. The study protocol is approved in all participating hospitals by the Medical Ethics Committee.

We hypothesise that nerve root decompression according to Gill is more (cost-)effective on the short term (12 weeks) and equally (cost-)effective on the long term (2 years). Equal effectiveness is defined as maximal 4 points difference on the RDQ score between decompression and instrumented fusion. Moreover, we will identify subgroup of patients who may benefit more of one of the allocated treatments.

### Patients

All patients between 18 and 70 years with sciatica or neurogenic claudication lasting more than 12 weeks, based on imaging proven (MRI and CT-scan) spondylolytic spondylolisthesis grade I or II, are eligible for this study. During the first visit to the neurological outpatient clinic, the patient's history will be taken and a standardized neurological examination will be performed. During this visit the surgeon will inform the patient on the pathology of spondylolytic spondylolisthesis and controversies in best surgical treatment for this condition. The study will be explained to the patient and in case of a positive reaction an appointment will be made with one of the research nurses as soon as possible. After informed consent, the patient will be randomised during the first visit at the research nurse once the in- and exclusion criteria are met (table 1). Various questionnaires, outcome measures and baseline variables will be recorded.

**Table 1 T1:** Selection criteria for trial eligibility

***Inclusion criteria:***
• Age 18–70 years
• Spondylolytic spondylolisthesis grade I or II
• Persistent sciatica or neurogenic claudication, with or without low back pain, lasting more than 3 months
• Operation indication
• Informed consent

***Exclusion criteria:***
• Spondylolytic spondylolisthesis grade III or IV
• Herniated disc on affected level, which requires discectomy
• Low back pain only
• Instability on dynamic X-ray (>3 mm)
• Progressive spondylolisthesis
• Previous surgery on affected level
• Extreme obesitas (BMI > 35)
• Severe osteoporosis/chronic use of steroids
• Severe comorbidity/contraindication for surgery
• Planned migration to another country on the short term
• Inadequate knowledge of Dutch language
• Pregnancy

### Randomisation procedure

Patients will be randomly allocated to nerve root decompression according to Gill, either unilateral or bilateral, or instrumented spondylodesis. The patient, surgeon, physiotherapist and research nurse are not blinded for the allocated treatment. Randomisation lists are prepared for every participating hospital separately using variable sized blocks of randomly allocated treatments to patients, sequentially numbered in order of inclusion, to ensure near-equal distribution of patients over the two randomisations arms in the hospitals. The data manager, who is not involved in the selection and allocation of patients, will prepare coded, sealed envelopes containing the treatment allocation. During the first visit of the research nurse, the envelope will be opened in presence of the patient and appointments will be made for the hospital admission. Surgery will be performed within 6 weeks after randomisation. Eligible patients who have a strong preference for one of the allocated surgical techniques, and are not willing to be randomised but are consenting to participation in the study, will be followed as a separate cohort.

Patients, who are randomised for nerve root decompression according to Gill and have persisting leg pain on the first follow-up moment at 12 weeks, are offered secondary instrumented spondylodesis. These patients will be analysed in the Gill group conform the intent-to-treat principle.

### Intervention

Patients will be randomised in nerve root decompression according to Gill, unilateral or bilateral (Group A), and decompression combined with instrumented spondylodesis (Group B).

#### (A) Decompression without spondylodesis; (hemi)Gill's procedure

A lumbosacral midline incision will be made and the paravertebral muscles will be dissected unilateral or bilateral, depending on the patients' symptoms. The spondylolytic lamina and the inferior articular process are removed, together with fibrocartilaginous mass of the pseudo-joint. In case of a unilateral procedure a vertical hemi-laminectomy will be performed; i.e. hemi-Gill. The affected nerve root(s) will be decompressed adequately, implicating a reduction of the superior articular process when necessary. The wound will be closed in layers with a suction drain when necessary.

#### (B) Decompression with instrumented spondylodesis

The above-described bilateral decompression will be performed in all patients. After performing bilateral discectomy, pedicle screws will be placed in the affected segment under fluoroscopic control. The intercorporal space will be filled with either a cage or autologous iliac crest, depending on the surgeon's preference. Sagittal alignment will be achieved and the screws will be fixed to the rods under slight compression. The wound will be closed in layers with a suction drain when necessary.

Various surgical findings will be documented: severity of nerve compression (none, moderate, severe, extreme), localisation of nerve root compression (lateral recess, parapedicular under the pseudo-joint, neuroforamen between slipped disc and pedicle, or a combination), aspect of the nerve root (normal, purple), aspect of the disc (normal, bulging, protrusion, extrusion, sequester, slipped disc), dural tear, nerve root damage, blood loss, duration of the procedure, judgment on placement of pedicle screws and intercorporal grafts. Postoperative time of mobilisation and length of hospital stay will also be documented.

### Baseline data

Baseline assessment includes demographics, hobbies, sports, work status, smoking status, back pain history, medical history and co-morbidity, body mass index, and neurological signs and symptoms. The patient's satisfaction at work will be registered. The treatment preference of patient, surgeon and research nurse will be assessed on a 5-point scale ranging from "strong preference for Gill's procedure" to "strong preference for instrumented spondylodesis". In any case all (clinical) outcome assessments will also be measured at baseline as far as they are applicable at that moment.

### Outcome assessment

Most symptomatic patients with spondylolytic spondylolisthesis report leg pain, low back pain and disability to perform normal daily activities. We will assess the below described validated outcome parameters. Patients will not be informed about their previous scores. Follow-up examination will take place at 6, 12, 26, 52, 104 and 260 weeks after randomisation. Additionally, at 3, 156 and 208 weeks after randomisation, questionnaires will be sent by mail (table 2).

**Table 2 T2:** Data collection and outcome measures.

***Time in weeks***	*X*	*0*	***3***	*6*	*12*	*26*	*52*	*104*	***156***	***208***	*260*
Preferred treatment of patient/surgeon/RN	v										
Neurological examination	v			v	v	v	V	v			v
Randomisation	v										
Operation		v									
Perceived recovery according to patient (Likert)	v		**v**	v	v	v	V	v	**v**	**v**	v
Perceived recovery according to surgeon/RN (Likert)				v	v	v	V	v			v
Macnab	v			v	v	v	V	v			v
HADS	v			v	v	v	V	v			v
Severity of complaints (VAS)	v	v	**v**	v	v	v	V	v	**v**	**v**	v
Roland Disability Questionnaire	v	v	**v**	v	v	v	V	v	**v**	**v**	v
Karasek	v			v	v	v	V	v	**v**	**v**	v
SF-36	v			v	v	v	V	v	**v**	**v**	v
EuroQol	v	v	**v**	v	v	v	V	v	**v**	**v**	v
Patient diary	v		**v**	v	v	v	V	v	**v**	**v**	v
CPK		v									
X-ray	v				v		V	v			v
MRI	v						V				
CT	v				v		V				
(Re)-operation			**v**	v	v	v	V	v	**v**	**v**	v
Complications		v			v		V	v			v

X is randomisation and 0 is operation. On week 3, 156, and 208 (bold columns), questionnaires will be sent by mail

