## Discussion

In this article, the rational and design of a RCT on cost-effectiveness of two surgical strategies for sciatica caused by low-grade spondylolytic spondylolisthesis are described. To our knowledge this is the first RCT comparing nerve root decompression according to Gill versus instrumented spondylodesis. Based on the literature, the clinical results of nerve root decompression alone and instrumented spondylodesis seem equivalent, although solid conclusions cannot be made because of various methodological flaws.

The Sciatica-Gill trial is designed to elucidate the controversy in best surgical treatment of patients with symptomatic spondylolytic spondylolisthesis grade I and II. Gill's procedure is a less invasive procedure, patients can return to work quickly and instrumented related complications are avoided. However, secondary instrumented spondylodesis might be necessary in patients with persistent or recurrent leg pain. Currently, most surgeons advocate primary instrumented fusion. Arguments in favour of intercorporal spondylodesis are prevention of progressive slippage, enlargement of the neuroforamen, reduction of dynamic nerve root compression due to instability, and possible influence of low back pain. Whether more invasive surgery with higher costs and complications warrants instrumented spondylodesis as primary treatment, can be debated. Therefore we postulate that nerve root decompression according to Gill is more (cost-) effective on the short term and equally (cost-) effective on the long term, compared to instrumented spondylodesis. Subgroup analysis might identify patient groups who will benefit more from one of the treatments. The inclusion period will run until medio 2010 and follow-up measurements will be completed in 2012.

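### Table 2 schedules no complications check between weeks 12 and 52 and none tied to a second operation, so a secondary fusion in the Gill arm is checked later than a primary fusion

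*Protocol article*

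**What the plan says.** The note under Table 2 (Protocol article, Outcome assessment) defines the first two columns: "X is randomisation and 0 is operation". There is no column for any later operation. The Complications row is marked at column 0 and at weeks 12, 52, 104 and 260. The (Re)-operation row is marked at every follow-up contact, week 26 included. The text above the table confirms that a week 26 visit is held: "Follow-up examination will take place at 6, 12, 26, 52, 104 and 260 weeks after randomisation".

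Under Randomisation procedure, Gill patients who "have persisting leg pain on the first follow-up moment at 12 weeks, are offered secondary instrumented spondylodesis". No such offer is described for the fusion arm. The same section continues: "These patients will be analysed in the Gill group conform the intent-to-treat principle".

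Two other sections bear on how harms are recorded. The Intervention section lists surgical findings such as dural tear, nerve root damage and blood loss, and adds: "Postoperative time of mobilisation and length of hospital stay will also be documented". It does not say whether this applies to a second operation. The Complications paragraph under Other outcome measures names patients, treating physicians and research nurses as the people who report complications, and gives no time window.

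**The concern.** The plan foresees that some Gill patients will undergo the comparator operation, and that they will be counted in the Gill arm. For the harms of the two strategies to be comparable, that operation should be followed as closely in one arm as in the other. The printed schedule does not do this. It places its two early complications checks around the first operation, and the offer of a second operation falls at the later of the two, after which nothing is scheduled until week 52.

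Complications are central to the comparison. The Background frames the trial as a trade-off between leg pain that persists or recurs after Gill and more complications and cost after fusion. The Discussion says of Gill that "patients can return to work quickly and instrumented related complications are avoided". A Gill-first strategy with a planned offer of fusion avoids those complications only in patients who are not fused later. If questions asked many months afterwards miss events, the missing events lie mainly in the Gill arm, and the complications comparison shifts towards the arm that the trial expects to do better.

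**Working it through.** The plan states no figure to reproduce here. The check is of intervals in the schedule.

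**Inputs from the article**
- Complications marks in Table 2: 0, 12, 52, 104, 260.
- (Re)-operation marks in Table 2: 3, 6, 12, 26, 52, 104, 156, 208, 260.
- Offer of secondary fusion: week 12, Gill arm.
- First operation: "Surgery will be performed within 6 weeks after randomisation".

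**Assumption.** The article gives no timing for the secondary operation. I borrow the 6-week limit that it sets for the first one, so the secondary fusion falls between week 12 and week 12 + 6 = 18. Week 26 is added as a later case.

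**Secondary fusion: weeks from operation to first check**

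| Operation at week | Table 2 as printed (next mark: week 52) | If week 26 were marked |
|---|---|---|
| 12 | 52 − 12 = 40 | 26 − 12 = 14 |
| 18 | 52 − 18 = 34 | 26 − 18 = 8 |
| 26 | 52 − 26 = 26 | no gain |

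**Primary fusion.** The first check is at the operation itself. The second is at week 12. If weeks run from the operation, that is 12 weeks after surgery. If they run from randomisation, with surgery 0 to 6 weeks later, it is 12 − 6 = 6 to 12 − 0 = 12 weeks after surgery.

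**Time origin.** The text counts visits from randomisation, while Table 2 sets the operation at 0. This can move the intervals by at most 6 weeks. Even 34 − 6 = 28 weeks is well beyond the 6 to 12 weeks for a primary fusion, so the conclusion does not depend on it.

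**Other scheduled contacts.** After week 12 the next X-ray and CT marks are also at week 52, so scheduled imaging does not fill the gap. Neurological examination and the patient diary are marked at week 26 and could bring some events to light. Neither is a complications check.

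**The case against.** The strongest reply is that Table 2 lists scheduled assessments and does not limit when a complication may be recorded. The Complications paragraph is open-ended: a surgeon who performs a secondary fusion could report a dural tear on the day. The surgical findings in the Intervention section are not confined to the first operation, and the Incidence of re-operations paragraph counts every re-exploration in both groups. The (Re)-operation row would identify the secondary fusion by week 26. The article is also a condensed account, and a per-operation case record form may exist.

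Much of this stands, and it rules out three stronger readings.

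- A reader might infer that harms are collected around the first operation only. The marks at weeks 52, 104 and 260 contradict that.
- A reader might infer that Gill harms are in fact undercounted. Open-ended reporting, and a week 52 question that can still reach back, mean that this is not shown.
- A reader might infer that the cost comparison is biased in the same way. The Costs paragraph provides three-month diaries that the nurse reviews at visits, and Table 2 marks the diary at week 26, so costs do not depend on the Complications row.

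It is also fair to add that the Discussion goes straight on to say that secondary fusion may be needed, so the authors do not hide it.

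The schedule itself remains open to criticism. The Complications paragraph says who reports, not when, and does not say whether a secondary fusion counts as the treatment to which a complication is attributed. The only stated timing is Table 2, which leaves week 26 blank for complications while filling it for re-operation. That is a feature of what is printed, not a detail left to a fuller document.

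**Conclusion.** The point holds as a risk of differential ascertainment. As printed, a secondary fusion at weeks 12 to 18 has its first scheduled complications check 34 to 40 weeks later, against a check at operation and another within about 12 weeks for the same operation done first. The interval rests on the assumed timing. The direction, favouring Gill on complications, depends on late questioning missing events that open-ended reporting does not catch. A fusion patient re-operated after week 12 meets the same gap, but the planned offer of a second operation exists in the Gill arm only.

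The number of events affected cannot be computed. It is tempting to take the 80% good-result rate in the Sample size section and infer 0.20 × 110 = 22 secondary fusions. That 80% is the rate needed to show superiority, not a forecast. The offer depends on persisting leg pain, a different criterion, and acceptance is unknown. With the 60% rate assumed for fusion, the same arithmetic gives 0.40 × 110 = 44. The article gives no complication risk for a secondary fusion either.

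The primary outcome is not affected. The matter still deserves correction, because complications are one side of the stated trade-off and the remedy is cheap.

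**What to change.** 1. Add a Complications mark at week 26 in Table 2. The visit already takes place. For an operation at weeks 12 to 18 the first check then comes 8 to 14 weeks afterwards.
2. Add a footnote to Table 2: for every operation in either arm, first or later, the surgical-findings form described under Intervention and a complications record are completed. This also covers operations after week 26, which the new mark alone would not help.
3. State that these complications are counted in the randomised arm and reported separately for the index operation and for re-operation.

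If continuous recording for any operation is already intended, a sentence saying so in the Complications paragraph would meet most of the point.

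The cost is one added item at an existing visit and some extra form completion for re-operated patients. No new visit or instrument is needed, and treatment is unchanged.
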